### Allocation and blinding

A minimization method is used with history of bDMARDs use (yes/no) and anti-cyclic citrullinated peptide antibody status (positive/negative). Eligible patients will be randomly assigned electronically by a central system in a 1:1 ratio to either the combination therapy group (Add-on group) or the group switched to filgotinib monotherapy (Switch group). This is an open-label trial with no blinding implemented.

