### Sample size calculation

Based on the results from the DARWIN1, DARWIN2, and FINCH3 trials, this study assumes a mean difference in change from baseline in DAS28-CRP at week 24 between the two groups of 0.07, with a standard deviation of 1.1. With an equal sample size ratio of 1:1 between the groups, and assuming a mean difference of 0.07, a standard deviation of 1.1, a one-sided significance level of 0.05, and a power of 80%, the required sample size was calculated to be 108 participants (54 per group). As for the sample size calculation, a one-sided test was employed based on the clinical assumption that filgotinib monotherapy would not be inferior to the combination of filgotinib and MTX. Considering a dropout rate of approximately 10%, the total sample size was set at 120 participants (60 per group).

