### Outcomes

#### Primary endpoint.

The primary endpoint is the change in DAS28-CRP from baseline at week 24, with the objective of determining if the Switch group is non-inferior to the Add-on group. The non-inferiority margin of 0.6 was adopted based on the study by Rubbert-Roth et al [12]. The value of 0.6 was derived by Rubbert-Roth and colleagues based on the meta-analysis results of treatment effects using DAS28 in patients with rheumatoid arthritis, as well as the fact that a change of 0.6 or less is internationally adopted in the EULAR response criteria as a threshold indicating no clinically significant change [13].

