### Statistical methods

For the primary endpoint, the change in DAS28-CRP from baseline will be analyzed using a Mixed Effects Model for Repeated Measures (MMRM). This method considers the baseline measurement as a covariate and incorporates group, time point, and the interaction between time point and group as fixed effects. It also reflects the variance-covariance structure of repeated measurements within each patient. Using this model, the least squares mean difference between groups at week 24 and its 90% confidence interval will be calculated. Non-inferiority will be confirmed if the upper limit of this 90% confidence interval is less than 0.6.

For the secondary endpoints, the proportion of patients meeting each endpoint and the corresponding 95% confidence intervals will be calculated. For the change from baseline in each endpoint, summary statistics (number of patients, mean, standard deviation, minimum, median, and maximum) will be presented. Additionally, the change from baseline will be analyzed using the same MMRM approach as for the primary endpoint, estimating the least squares mean and its 95% confidence interval at each time point.

As a sensitivity analysis, stratification will be performed based on stratification variables (history of bDMARD use and anti-CCP antibody positivity/negativity), and summary statistics will be calculated for baseline values, measurements at each time point, and changes from baseline by treatment group and treatment period, with intergroup comparisons conducted using t-tests.

Additionally, as a supplementary analysis, in the PPS population, intergroup comparisons of changes from baseline will be conducted using MMRM, and summary statistics will be calculated with intergroup comparisons performed using t-tests. Furthermore, in the PPS population, stratification based on the aforementioned stratification variables will be conducted, and summary statistics will be calculated for baseline values, measurements at each time point, and changes from baseline by treatment group and treatment period, with intergroup comparisons conducted using t-tests.

For the cumulative values of CRP and MMP-3, the AUC for each participant will be calculated, and summary statistics (number of patients, mean, standard deviation, minimum, median, and maximum) for each group will be presented.

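### The primary MMRM leaves out both minimisation factors, so the non-inferiority test is mildly conservative if those factors are prognostic beyond baseline DAS28-CRP

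*Protocol article*

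**What the plan says.** Allocation and blinding: "A minimization method is used with history of bDMARDs use (yes/no) and anti-cyclic citrullinated peptide antibody status (positive/negative"). Assignment is central, electronic and 1:1.

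Statistical methods gives the primary model term by term. On the covariate: "This method considers the baseline measurement as a covariate". The model also "incorporates group, time point, and the interaction between time point and group as fixed effects", with a within-patient covariance structure. The result is a least-squares mean difference at week 24 with a 90% confidence interval. Non-inferiority is declared if the upper limit lies below 0.6. The same MMRM approach is applied to secondary changes from baseline, and an MMRM is also run in the PPS.

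The minimisation factors come back later in the same section: "As a sensitivity analysis, stratification will be performed based on stratification variables (history of bDMARD use and anti-CCP antibody positivity/negativity"). That analysis consists of summary statistics and t-tests between groups, and it is repeated in the PPS.

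Sample size calculation plans for "a one-sided significance level of 0.05, and a power of 80"%, "assuming a mean difference of 0.07, a standard deviation of 1.1". It mentions no covariate adjustment.

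**The concern.** Minimisation removes most of the chance imbalance between arms on the two factors. If the factors predict the outcome, the treatment difference therefore varies less from trial to trial than under simple randomisation. A model without the factors cannot see this. Their variance stays in the residual, and the reported standard error is larger than the true one.

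The primary conclusion rests on a single comparison, the upper 90% limit against 0.6. A standard error that is too large makes the interval cover more than 90% and the test run below its nominal 5%. It also gives up some precision that the allocation has already secured.

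The stratified t-tests do not make up for this. They compare arms within subsets of about 120 patients and produce no overall factor-adjusted interval for the 0.6 margin.

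**Working it through.** **Inputs from the protocol.** Margin: "The non-inferiority margin of 0.6 was adopted". Assumed true difference 0.07, SD 1.1, one-sided alpha 0.05, power 80%, 54 per arm evaluable, dropout about 10%.

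**Assumed, not in the protocol.** R², the share of week-24 variance left after baseline that the two factors explain together, is taken as 3% to 20%. Balance on the factors is taken as near perfect. SD 1.1 is treated as the residual SD of the model without the factors. A single week-24 comparison stands in for the MMRM contrast.

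**Step 1: reproduce the plan.** Distance to the margin: 0.6 − 0.07 = 0.53. n per arm = 2 × 1.1² × (1.645 + 0.842)² / 0.53² = 53.3, rounded up to 54, or 108 in total; 108 / 0.9 = 120. Both figures agree with the protocol.

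**Step 2: effect of leaving the factors out.**
- Reported SE = 1.1 × √(2/54) = 0.2117, so the 90% half-width is 1.645 × 0.2117 = 0.348.
- Actual SE under balanced allocation = 0.2117 × √(1 − R²).
- One-sided error at the margin = Φ(−1.645 / √(1 − R²)); coverage = 1 − 2 × that error.
- Power, factors omitted = Φ((0.53 − 0.348) / actual SE).
- Power, factors included = Φ(0.53 / actual SE − 1.645).

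| R² | Half-width omitted / included | Coverage, omitted | One-sided error, omitted | Power omitted | Power included | Points forgone |
|---|---|---|---|---|---|---|
| 0% | 0.348 / 0.348 | 90.0% | 5.0% | 80.5% | 80.5% | 0 |
| 3% | 0.348 / 0.343 | 90.5% | 4.7% | 80.8% | 81.5% | 0.7 |
| 5% | 0.348 / 0.339 | 90.9% | 4.6% | 81.1% | 82.2% | 1.1 |
| 10% | 0.348 / 0.330 | 91.7% | 4.15% | 81.7% | 84.0% | 2.3 |
| 20% | 0.348 / 0.311 | 93.4% | 3.3% | 83.1% | 87.6% | 4.4 |

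**Step 3: check by simulation.** Minimisation was simulated with a biased coin of 0.8, N = 108, 6,000 trials per setting, and assumed prevalences of 30% prior bDMARD use and 75% anti-CCP positive. At R² 10%, power was 81.3% omitted and 83.2% included, with error 4.2% and 5.0%. At R² 20%, power was 82.3% and 86.9%, with error 3.5% and 5.3%. Under simple randomisation with the factors omitted, error stayed close to 5% (4.8% and 5.2% at the same R² values). The conservatism therefore comes from pairing minimisation with an unadjusted model.

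**Step 4: which R² is plausible.** For two independent factors that each shift week-24 change by d, R² × 1.1² = d² × (0.30 × 0.70 + 0.75 × 0.25) = 0.3975 d².
- R² 3%: d = √(0.0363 / 0.3975) = 0.30.
- R² 10%: d = √(0.121 / 0.3975) = 0.55.
- R² 20%: d = √(0.242 / 0.3975) = 0.78. With both prevalences at 50% it is still √(0.242 / 0.5) = 0.70.

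The top of the range thus requires each factor, after baseline adjustment, to move the outcome by more than the 0.6 that the protocol treats as the limit of no clinically significant change.

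**The case against.** **A statistical analysis plan that is not shown could add the terms.** This carries little weight. The article is not silent: it names the covariate, the fixed effects, the contrast, the interval and the decision rule. The list reads as complete, and it lacks the allocation factors.

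**The plan still delivers what it promised.** This stands in full. A reader might infer that the trial is underpowered, or that its 5% level is wrong in a harmful direction. The figures support neither. With the factors omitted, power is 80.5% or more across the whole range and rises with R². One-sided error is at or below 5%, so a false claim of non-inferiority becomes less likely. The loss exists only against a better model.

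**The size is speculative.** This largely stands. No R² is given, and what counts is the part beyond baseline DAS28-CRP, which the model already includes. The high end needs large factor effects (Step 4). Choosing these factors for balancing suggests that the investigators expect some prognostic value, but not how much.

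**Near-perfect balance is a best case.** This also stands. The protocol does not say how deterministic the minimisation is, and dropout of about 10% loosens balance at week 24. The biased-coin simulation gave a gain of 1.9 points at R² 10%, against 2.3 from the formula. The same loosening is a reason to adjust, because the unadjusted model does not correct imbalance that arises after allocation.

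**Conclusion.** The point holds as a minor matter of efficiency and consistency between design and analysis. The primary model omits both factors on which allocation is minimised, and no other planned analysis supplies an overall factor-adjusted 90% interval for the margin. If the factors are prognostic beyond baseline, the interval is about 1.5% (R² 3%) to 11.8% (R² 20%) wider than it need be, with the coverage, error and power shown in the table. An effect near the low end is more likely. If the factors add nothing beyond baseline, there is no effect. The omission is certain from the text; its size rests on the assumed R², near-perfect balance and the single-visit approximation. The sample size of 120 and the 5% error bound stand.

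**What to change.** Add prior bDMARD use (yes/no) and anti-CCP status (positive/negative) as fixed effects to the primary MMRM. Preferably include the interaction of each with time point: a main effect alone forces the same factor effect at every visit and may not recover the full gain at week 24. Make the same change to the MMRM for secondary changes from baseline and to the PPS MMRM. The stratified t-tests can stay as descriptive support.

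The cost is one sentence of analysis wording and two degrees of freedom, or two per visit with the interactions. No new data are needed, since allocation already requires both variables. The article reports enrolment as ongoing and data fixing in March 2027, so the change can be made before database lock. In an open-label non-inferiority trial, an adjustment chosen after the data have been seen would be open to challenge.

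### The only analysis labelled sensitivity, and the t-test parts of the per-protocol analysis, are not tied to the 0.6 margin and do not test the primary model's assumptions

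*Protocol article*

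**What the plan says.** All of this is in the Protocol article, mainly under Statistical methods.

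- **Primary analysis.** The MMRM has baseline as a covariate and group, time point and their interaction as fixed effects. The decision rule is explicit: "Non-inferiority will be confirmed if the upper limit of this 90% confidence interval is less than 0.6".
- **Sensitivity analysis.** "As a sensitivity analysis, stratification will be performed based on stratification variables", namely history of bDMARD use and anti-CCP status. Baseline values, measurements and changes are summarised by group, and the arms are compared with t-tests.
- **Supplementary analysis in the PPS.** It has three parts. The first is an MMRM comparison of change from baseline. Next, "summary statistics will be calculated with intergroup comparisons performed using t-tests". Last come the same stratified summaries and t-tests within the PPS.

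No margin, confidence interval or covariate is attached to any of the t-tests. The 90% interval and the 0.6 rule are not repeated for the PPS MMRM.

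Three other sections bear on this. Per protocol set (PPS) describes that set as the one for sensitivity analysis of efficacy. Statistical methods says missing data at each time point will not be imputed. The Discussion states that MMRM is valid only under missing at random, that this cannot be verified from the data, and that further sensitivity analyses, not specified, will be explored.

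**The concern.** A robustness check for a non-inferiority claim should ask the primary question again under a changed population or assumption. These t-tests depart from that in three ways.

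1. **Hypothesis.** With no shifted null stated, a t-test between arms addresses zero difference. A non-significant result does not show that the deficit is below 0.6, and a significant one does not show that it exceeds 0.6.
2. **Assumptions.** Splitting by bDMARD history or anti-CCP status changes the subset analysed. It leaves the missing-at-random assumption, which the Discussion itself flags, untested. A t-test at week 24 without imputation uses only patients observed at that visit. It therefore gives up both the baseline adjustment and the MMRM's use of earlier visits.
3. **Precision.** The trial expects about 108 evaluable patients, so the smaller level of either factor may leave few patients per arm.

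At stake is how the supporting evidence is interpreted. A row of non-significant p-values under the heading of sensitivity analysis could look like corroboration when it carries little information about the margin.

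**Working it through.** **Inputs.** The margin of 0.6 is from Primary endpoint. The rest is from Sample size calculation: "assuming a mean difference of 0.07, a standard deviation of 1.1, a one-sided significance level of 0.05, and a power of 80" per cent, 1:1 allocation, 54 per group evaluable, and 60 per group after about 10% dropout.

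**Step 1: reproduce the plan's figure.**
n per arm = 2 × (1.645 + 0.842)² × 1.1² / (0.6 − 0.07)² = 53.3, rounded up to 54, so 108 in total. 108 / 0.9 = 120. Both figures agree with the plan. Power from the non-central t distribution at 54 per arm is 80.0%.

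**Step 2: compare the two decision rules at 54 per arm.** This is a two-sample approximation without the precision that baseline adjustment may add. Differences are Switch minus Add-on, with positive values unfavourable to Switch, as the upper-limit rule implies.
- SE = 1.1 × √(2/54) = 0.2117, with 106 degrees of freedom.
- Non-inferiority is met if the observed difference is below 0.6 − 1.659 × 0.2117 = 0.6 − 0.351 = 0.249.
- A two-sided 5% t-test of zero difference is non-significant if the absolute difference is below 1.983 × 0.2117 = 0.420.

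An observed difference between about 0.25 and 0.42 therefore fails the primary rule while the t-test reports no significant difference.

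**Step 3: chance of non-significance when the true deficit is the whole margin.** Non-centrality = 0.6 / (1.1 × √(2/n)), df = 2n − 2, two-sided 5%. The document gives no prevalence for either factor, so every n below 54 is an assumed stratum size with equal arms.

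| n per arm | Non-centrality | P(non-significant) |
|---|---|---|
| 54 | 2.83 | 20% |
| 43 | 2.53 | 30% |
| 30 | 2.11 | 45% |
| 27 | 2.00 | 50% |
| 20 | 1.72 | 61% |
| 15 | 1.49 | 70% |
| 11 | 1.28 | 77% |

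A factor split 80/20 would give about 43 and 11 per arm, and an even split gives 27 and 27. At 27 per arm the 90% half-width is 0.50. At 11 it is 0.81, wider than the margin.

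**Step 4: set the planned checks against the primary analysis.**

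| Check | Baseline-adjusted, repeated measures | 0.6 margin stated | What it changes |
|---|---|---|---|
| Stratified t-tests (labelled sensitivity) | None stated | No | Subset only |
| PPS MMRM | Same type of model as the primary | Not restated | Population |
| PPS t-tests | None stated | No | Population and method |
| PPS stratified t-tests | None stated | No | Population, subset and method |

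Only the second row is a direct counterpart of the primary analysis.

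**The case against.** The best defence is that the check that matters most in a non-inferiority trial, an MMRM in the per-protocol set, is already planned. The non-inferiority conclusion is tied to one rule on the primary MMRM, and nothing in the article says that a non-significant t-test will count as support. The null hypothesis of the t-tests is not stated. Further sensitivity analyses are promised, and their detail may properly sit in an analysis plan that is not shown.

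Much of this stands, and it rules out several stronger readings:

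- A reader might infer that all the robustness checks are t-tests. The PPS MMRM shows otherwise.
- A reader might infer that the authors intend non-significance as evidence of non-inferiority. The text does not say so; the risk is one of later interpretation.
- A reader might infer that the strata will usually give p > 0.05 even at a full 0.6 deficit. That holds only below about 27 per arm. The larger level of a factor could keep most patients, and the article does not say that the two factors are crossed.
- A reader might extend the point to the responder endpoints, for which "the proportion of patients meeting each endpoint and the corresponding 95% confidence intervals will be calculated" with no between-arm difference mentioned. That is a separate reporting matter for descriptive secondary endpoints and can be left to the analysis plan.

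The defence does not meet the core of the point. The article does not leave the sensitivity method open. It names t-tests within strata, so an analysis plan that followed it would carry the same weakness. A zero null is the ordinary meaning of a t-test between arms when no other null is given.

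**Conclusion.** The point holds in a limited form. The one analysis labelled sensitivity is a subgroup summary. Its t-tests, like those in the PPS, cannot confirm or challenge a claim about a 0.6 margin. The two rules disagree for observed differences of about 0.25 to 0.42 at 54 per arm. At a true deficit of 0.6, the t-test is non-significant about 20% of the time with all evaluable patients, and about 45% and 70% at 30 and 15 per arm.

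These figures assume SD 1.1, equal arms, a two-sided 5% test of zero difference and, below 54 per arm, stratum sizes that the document does not give. The sample size reproduces, and the primary model, margin and decision rule are not in question. The weakness lies in how the claim is checked and should be corrected before the data are analysed.

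**What to change.** 1. **PPS.** State that the PPS MMRM reports the week-24 least squares mean difference with its 90% confidence interval, read against 0.6 as in the primary analysis. Drop the PPS t-tests.
2. **Strata.** Replace the stratified t-tests with one MMRM that includes treatment-by-stratum (by visit) terms. Report the week-24 difference in each stratum with its confidence interval.
3. **Label.** Present the stratum results as descriptive subgroup results, not as a sensitivity analysis.

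The cost is revised wording and a few extra model runs, with no new data and no change to the sample size or primary rule. The drawback is wide intervals in the smaller strata, but these show openly what a non-significant p-value would hide.

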The rate of CRRP and RRP at week 24 and week 48 will be analyzed. The denominator for the proportion will be the number of FAS in each group, with the numerator for the CRRP rate being the number of cases with an mTSS increase of 3 or more at week 24 and 48, and the numerator for the RRP rate being the number of cases with an mTSS increase of 5 or more at week 24 and 48.

8) Cumulative values of CRP and matrix metalloproteinase (MMP)-3

The cumulative values of CRP and MMP-3 will be analyzed, with definition as the area under the curve (AUC) for CRP and MMP-3 for each subject.

9) Work productivity and activity impairment (WPAI)

WPAI at week 24 and week 48 will be analyzed. At week 24, summary statistics will be calculated for baseline values, measurements at each time point (week 24 and week 48), and changes from baseline in the two groups (Add-on group and Switch group). At week 48, the analysis will include four groups (Add-on to Switch group and Switch to Add-on group in addition to the original two groups).

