For the safety analysis, treatment-emergent adverse events (TEAEs) observed during the period from the start of the study treatment to the end of the observation period will be summarized. Adverse events that cannot be ruled out as being causally related to the study treatment will be classified as adverse drug reactions. For each group, the number and percentage of cases of TEAEs and adverse drug reactions will be summarized by system organ class and preferred term. Additionally, a summary by severity level will also be provided.

Missing data at each time point will not be imputed. For patients who discontinue the study, only the data obtained up to the point of discontinuation will be used for analysis. Additionally, when analyzing the proportion of patients who achieve the endpoint, cases with missing data at each time point, including those who discontinued the study, will be considered as non-responders and included in the denominator.

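### Cumulative CRP and MMP-3 are AUCs cut off at discontinuation, so an arm with more or earlier dropout can look better on this secondary descriptive endpoint

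*Protocol article*

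**What the plan says.** Item 8 under Secondary endpoints covers cumulative CRP and MMP-3, "with definition as the area under the curve (AUC) for CRP and MMP-3 for each subject". Statistical methods repeats this, "For the cumulative values of CRP and MMP-3, the AUC for each participant will be calculated", and follows it with descriptive statistics for each group, the mean and median among them.

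The missing-data paragraph at the end of Statistical methods applies generally. It says "Missing data at each time point will not be imputed", and for patients who leave, "only the data obtained up to the point of discontinuation will be used for analysis". Its one protective rule, counting missing cases as non-responders, is confined to proportions: "when analyzing the proportion of patients who achieve the endpoint, cases with missing data at each time point". It does not reach the AUC.

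The full analysis set is the efficacy population. It includes every patient who took filgotinib and has at least one measurable efficacy point, so early leavers stay in. The article does not divide the AUC by time observed, set a common window for it, or limit it to completers.

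**The concern.** An area under a curve grows with the length of the curve. Under the stated rules, a patient followed for 12 weeks supplies 12 weeks of area and is averaged with patients who supply the full period. The group mean then mixes two things: how inflamed patients were, and how long they were observed.

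Leaving may also be related to inflammation. The section on prohibited therapies bars other csDMARDs, bDMARDs and other JAK inhibitors during study treatment. The withdrawal criteria remove patients who wish to stop, or whose treatment is interrupted for more than 28 consecutive days. A patient whose disease is not controlled can therefore end follow-up early, and the high values that would have followed never enter the AUC.

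At stake is the reading of this endpoint. A lower mean would be taken as less cumulative inflammation when part of it may only be less follow-up.

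**Working it through.** **Figures in the article.** No figure is given for this endpoint. The relevant inputs are the 48-week intervention period, the week-24 comparison point and the planned dropout of about 10% (Sample size calculation). The article gives no timing of dropout and no split by arm, so those are assumed below.

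**Direction.** CRP and MMP-3 cannot be negative. Removing the part of the curve after discontinuation can only reduce a patient's area or leave it unchanged. This holds whatever the profile.

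**One arm, constant CRP.** If a fraction p stops at week d of a window of H weeks, the mean AUC falls by p × (1 − d/H). With p = 0.10 and d = 12 (assumed):
- H = 24: 0.10 × (1 − 12/24) = 5%
- H = 48: 0.10 × (1 − 12/48) = 7.5%

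**Two arms, identical constant CRP of 1.** Mean AUC = (1 − p) × H + p × d. For H = 48, d = 12, the 5% arm has 0.95 × 48 + 0.05 × 12 = 46.2 and the 15% arm has 0.85 × 48 + 0.15 × 12 = 42.6. The gap is 42.6/46.2 − 1 = −7.8%. The other cases:

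| Window | Stop at week | Mean, 5% dropout | Mean, 15% dropout | Gap | Gap, 5% vs 20% |
|---|---|---|---|---|---|
| 24 weeks | 4 | 23.0 | 21.0 | −8.7% | −13.0% |
| 24 weeks | 8 | 23.2 | 21.6 | −6.9% | −10.3% |
| 24 weeks | 12 | 23.4 | 22.2 | −5.1% | −7.7% |
| 48 weeks | 4 | 45.8 | 41.4 | −9.6% | −14.4% |
| 48 weeks | 8 | 46.0 | 42.0 | −8.7% | −13.0% |
| 48 weeks | 12 | 46.2 | 42.6 | −7.8% | −11.7% |

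With 10% dropout in both arms at the same week, the gap is 0 in every row, although both means are too low.

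**Individual patients (assumed profiles, trapezoidal rule, assumed visits at weeks 0, 4, 8, 12, 24, 36, 48).** A responder with CRP 2.0, 1.0, 0.7, then 0.5 mg/dL throughout has AUC 6.0 + 3.4 + 2.4 + 3 × 6.0 = 29.8 over 48 weeks. A non-responder constant at 2.0 has 8.0, 16.0 or 24.0 if leaving at week 4, 8 or 12, against 96.0 with full follow-up. In this example each of those early leavers scores below the responding completer. The same non-responder leaving at week 24 has 48.0, which is above the completer.

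**Does dividing by observed time cure it?** For the flat non-responder, yes: 2.0 at any exit time, against 29.8/48 = 0.62 for the completer. For a responder who leaves at week 12, no: the area is 6.0 + 3.4 + 2.4 = 11.8, and 11.8/12 = 0.98. The same patient staying to week 48 scores 0.62. Time-averaging gives too much weight to the high early values.

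**The case against.** The strongest reply is that an article leaves AUC derivation to the full protocol or analysis plan. Neither the formula nor the window is given here, and a time-standardised AUC or a missing AUC for incomplete profiles is not expressly excluded. That stands as far as it goes: absence of a formula is no finding, and unshown documents may already settle the matter. But the rules that are stated (AUC per patient, group summary, no imputation, data used up to discontinuation) lead to the truncated area when followed as written. Treating incomplete profiles as missing would also sit badly with the rule on using data up to discontinuation.

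Three stronger readings are tempting, and the documents do not support them.
- A reader might infer that the endpoint will rank the arms wrongly. That needs dropout unequal in amount or timing, or dropout related to CRP differently by arm. The article gives one dropout figure for the whole trial.
- A reader might let only non-responders leave and obtain a larger loss. Such a figure rests on CRP profiles that the article does not give, and it compares an arm with itself without dropout, not one arm with the other. Nor do all early leavers fall below completers, as the week-24 case shows.
- A reader might infer that the AUC runs to week 48 and so blends regimens after MTX changes. The article states no end point for the AUC. For WPAI, under Secondary endpoints, the authors handle the issue by using four groups at week 48.

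The consequence is also limited. No between-group test of the AUC is planned, the median is reported with the mean, and change from baseline in CRP and MMP-3 at each time point is listed under Other efficacy endpoints.

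**Conclusion.** The point holds in limited form. The stated rules average areas over unequal follow-up, and truncation lowers the AUC of those who stop early. The arm with more or earlier dropout can therefore look better on cumulative CRP and MMP-3.

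Under constant CRP, planned-size dropout placed at week 12 costs an arm 5% to 7.5% of its mean AUC. Dropout of 5% versus 15% at weeks 4 to 12 produces a gap of about 5% to 10% between arms with identical CRP. The direction of truncation is certain. The sizes depend on assumed dropout timing, split and CRP profile, and the gap vanishes when dropout is equal in amount and timing under identical CRP.

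The endpoint is secondary and descriptive. The DAS28-CRP non-inferiority conclusion does not depend on it. The wording should be changed, but it does not threaten the trial.

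**What to change.** State a fixed window for the AUC. Use baseline to week 24 for the comparison between arms, because the protocol allows MTX to change in both arms afterwards. If a 48-week AUC is also shown, say how patients who changed MTX are grouped.

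Derive each group's AUC, and the difference with its confidence interval, from MMRM visit means of CRP and MMP-3 over that window. This is a linear combination of visit means. With visits at weeks 0, 4, 8, 12 and 24 (assumed, since the schedule figure is not shown), the trapezoidal weights are 2, 4, 4, 8 and 6, which sum to 24. Every arm is then assessed over the same length of time, early leavers still contribute what was observed, and no values are imputed. The result relies on missing at random, which the Discussion already acknowledges for MMRM.

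The AUC divided by observed time may be added as a supplementary summary, with a note that it overweights high early values in responders who leave early. A log scale is optional.

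The cost is a sentence or two of analysis wording and a model fit for each marker, using the model form the article already specifies. No new data are needed, and data fix is planned for March 2027, so the wording can be settled before then.
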